## Abstract

**Background:**

Poststroke delirium (PSD) is a severe complication in patients with acute stroke and is characterized by rapid onset fluctuating symptoms, which affect multiple domains (cognition, motor system, and sleep-wake cycle). Similar to other types of delirium, PSD is associated with longer hospitalization, higher mortality, and a higher disability rate. Behavioral studies on cognitive functioning showed significantly poorer cognitive outcomes in both patients with and without PSD compared to healthy controls. Thus, the distinction between “stroke-related” and “PSD-related” cognitive impairments remains unclear. A frequently affected and highly disabling cognitive domain is memory function. However, imaging studies, particularly task-based functional magnetic resonance imaging (MRI) studies on PSD, are currently scarce and represent a significant gap in the existing literature.

**Objective:**

This longitudinal proof-of-concept study aims to investigate the short- and long-term effects of stroke and PSD on cognitive outcome using a multimodal approach and to outline a protocol for a repeated multimodal cognitive assessment in patients with stroke.

**Methods:**

We developed a longitudinal study protocol to investigate short- and long-term effects of stroke and PSD on cognitive impairment and recovery. Poststroke cognitive impairment (PSCI) will be assessed in a comprehensive digital multimodal approach including a multidomain neuropsychological app to facilitate a standardized, rapid testing, particularly for long-term outcomes, as well as task-based functional MRI (introducing a modified working memory task) during the acute (prior PSD development) and postacute phase post stroke and at a 3-month follow-up. In total, 40 patients with acute stroke, divided into a PSD group and non-PSD group (control), will be examined. In the context of the proof-of-concept study, the eligibility of a modified working-memory task, an app-based neuropsychological assessment, and a multimodal MRI protocol will be evaluated. The primary endpoint is a between-group comparison of the cognitive outcome, defined as global PSCI at a 3-month follow-up. Global PSCI will be classified as normal cognitive functioning, or mild, moderate, or severe cognitive impairment, according to the performance level (norm-referenced *z* scores) on a multidomain neuropsychological assessment.

**Results:**

This study was funded in December 2023. As of May 2025, 15 patients with stroke have been included. Recruitment and data collection were initiated in June 2024 and are ongoing until December 2025. The findings are expected to be published in summer 2026.

**Conclusions:**

This protocol outlines a proof-of-concept study aiming to fill a critical gap by systematically investigating cognitive functions in patients with acute stroke with and without delirium. Generating reliable preliminary data will provide essential groundwork for future large-scale research, ultimately enhancing understanding of the contribution of PSD to cognitive impairment.

## Introduction

Delirium is an acute clinical condition characterized by a wide range of symptoms affecting multiple domains. Patients with delirium often present with attention deficits, confusion, hallucinations, agitation, or disturbances in sleep-wake cycle. Typically, delirium occurs during critical illness, such as after surgery or stroke, with rapid onset and fluctuating symptoms [1]. Poststroke delirium (PSD) is one of the most common complications after stroke, with reported prevalence rates reaching up to 40% in older patients [1-3]. Both delirium in general and PSD in particular are associated with longer hospitalization, higher mortality, accelerated cognitive decline, and lower quality of life [1,4-11]. There is a broad consensus of a multifactorial origin [1,12,13], with predisposing factors such as dementia, age, comorbidities, and precipitating risk factors, including infection, stroke, or surgery [1,12,13]. The presence of multiple and fluctuating symptoms is diagnostically challenging, especially in patients with stroke with communication difficulties (eg, aphasia), and requires clinical expertise and standardized screening tools, such as the well-established ICDSC (Intensive Care Delirium Screening Checklist) [14,15]. Despite the high prevalence and the nondeclining mortality rate over the past decades [2,7], objective diagnostic tools and prognostic biomarkers (ie, fluid or proteomic biomarkers), as well as protective markers for long-term cognitive outcome, have not yet been implemented in clinical practice and remain the focus of ongoing studies [5,16-18].

In general, examining delirium patients is a challenging field, which limits the number of available studies. Patients with delirium, such as patients with PSD, represent a vulnerable and critically ill population. Especially during the acute (within 5 d poststroke) and the postacute phase (5 d to 12 wk poststroke), patients may experience secondary deteriorations or be scheduled for invasive diagnostic procedures or surgeries, making the conduction of studies difficult. Additionally, the fluctuating nature of delirium symptoms complicates the timing and consistency of study assessments. Furthermore, during the acute state of delirium, especially cases involving high arousal or hallucinating symptoms, cognitive assessment or magnetic resonance imaging (MRI) assessment becomes impossible, as patients cannot comply with task instructions. This results in a lack of studies and underscores the need for further research in this area. Another challenge in this field concerns the study design, varying with regard to concurrent versus sequential study designs, as well as the choice of an appropriate control group.

Previous studies have reported a higher risk of PSD in total anterior circulation infarcts compared to partial anterior, posterior, and lacunar infarcts [19-21]. Cortical networks in the anterior circulation, such as fronto-parietal networks, are known to be involved in higher-level cognitive functions, including executive functions, attention, and memory. These very cognitive domains are affected in PSD. Memory functions, which represent a critical component of human cognition, are frequently affected and represent a highly disabling cognitive domain in stroke survivors [22]. For example, memory impairments have been significantly associated with poor quality of life of patients with stroke and their caregivers, for example, [22,23], demonstrating the high relevance to daily life and potential burden. Moreover, memory assessment is a well-established component of both neuropsychological testing and in functional magnetic resonance imaging (fMRI) studies, making it an ideal focus for our study.

In the challenging field of cognitive assessment in patients with delirium, the majority of studies focus on behavioral measures including the assessment of multiple cognitive domains such as attention, language, memory, executive functions, and visuospatial construction. Previous studies have demonstrated a significantly poorer cognitive outcome (eg, global cognition and executive functions) in patients with postdelirium compared to healthy controls [24-26].

Additionally, advanced techniques such as MRI have been implemented to provide further insights. Structural MRI studies, which do not require a certain level of patients’ compliance, have reported abnormalities in white matter tracts of patients with postdelirium, which are known to be involved in memory and attention [1,13,27]. Since delirium is known to be a disorder of disrupted brain networks [1,12,16,28,29], fMRI studies, which were predominantly conducted as resting-state studies in patients with postdelirium, have demonstrated aberrant connectivity in dorsal prefrontal and subcortical regions compared to healthy controls, which may contribute to the emergence of delirium symptoms [13,28,30]. These findings in network dysfunctions are restricted to the default mode network, and memory functions may not be detected during resting-state fMRI [31]. An essential requirement for studying memory functions and related activity or connectivity dysfunctions in delirium is a memory task-based fMRI study. Unfortunately, these are exceedingly limited.

To date, only 1 fMRI study has been conducted, using a well-known N-Back working memory task [32]. While reporting no association between delirium and brain region activity, several methodological limitations and concerns have been raised, such as the infeasibility of the working memory task (especially at the time of discharge), the infeasible MRI protocol, as well as the absence of a control group. Of note, connectivity analyses have not been conducted. Further research is therefore needed, alongside the development of an adequate and reliable task for working memory assessment during fMRI.

An additional challenge in studying PSD and cognitive outcomes is the unresolved distinction between PSD-related and pure stroke−related cognitive impairments. In detail, cognitive deficits associated with PSD and other types of delirium, for example, attention or memory deficits, have also been reported in patients with stroke without PSD [23]. Previous imaging studies have shown reduced brain activation as well as abnormal connectivity within fronto-parietal networks in patients without PSD compared to healthy controls [31,33,34]. Thus, the origin of cognitive impairments in patients with PSD (ie, distinction between “stroke-related” vs “PSD-related” impairments) remains unclear.

To summarize, there is a lack of reliable and feasible fMRI tasks for assessing memory functions in patients with PSD. The few existing task-based fMRI studies have either been conducted without control groups or have only compared groups of patients with PSD to healthy controls, limiting the ability to disentangle the distinct cognitive and neural contributions of PSD versus stroke. Therefore, there is a significant gap in the literature regarding appropriate methods to study PSD and its cognitive outcomes, emphasizing the need for comprehensive, longitudinal investigations that combine neuropsychological assessments with functional neuroimaging.

To address this gap, we present a protocol for a comprehensive longitudinal proof-of-concept study that aims to systematically and comprehensively examine poststroke cognitive impairment (PSCI) in a critically ill stroke population, both with and without PSD (control group). Assessments will be conducted during the acute (within 5 d post stroke) and postacute phases (5‐14 d post stroke), and at a 3-month follow-up using a multicomponent neuropsychological assessment and task-based fMRI. Generating reliable feasibility and preliminary data through this approach will provide essential groundwork for future multicenter studies.

The specific objectives of this study are to (1) compare the global PSCI of patients with and without PSD at a 3-month follow-up, (2) compare domain-specific cognitive outcome measures of patients with and without PSD at a 3-month follow-up, (3) generate preliminary data regarding the differentiation between PSD-related and stroke-related cognitive impairment using behavioral and fMRI connectivity measures, and (4) contribute toward developing protective and prognostic tools for the early detection and treatment of PSD.

## Methods

### Study Design and General Procedures

We present a protocol of the RECOVER (Cognitive Recovery After Poststroke Delirium) study, which is a monocenter study following a longitudinal design with 3 measurement points (S1-S3) and an individual trial duration of 3 months (Figure 1).

**Figure 1. F1:**
[figure not shown]
Overview of the RECOVER (Cognitive Recovery After Poststroke Delirium) study procedures. DSM-5: *Diagnostic and Statistical Manual of Mental Disorders, Fifth Edition*; DTI: diffusion tensor imaging sequence; FLAIR: fluid-attenuated inversion recovery sequence; ICDSC: Intensive Care Delirium Screening Checklist; MPRAGE: T1-weighted magnetization prepared rapid acquisition with gradient echoes sequence; MRI: magnetic resonance imaging; NIHSS: National Institutes of Health Stroke Scale; S1: session 1; S2: session 2; S3: session 3; T2*: T2-weighted echo planar imaging sequence; WM: working memory.

The three measurement points are as follows:

S1 during the acute phase poststroke (≤48 h after hospital admission; ≤96 h after stroke onset and before PSD development)S2 during the postacute phase poststroke (5‐14 d poststroke, depending on delirium recovery)S3 follow-up at 3 months poststroke (approximately 90 d poststroke)

Patients with stroke will be admitted to the Stroke Unit where a screening visit will be conducted, including a review of the inclusion and exclusion criteria. Following the review, written informed consent will be obtained from the patient or, if applicable, the legal guardian. Once consent has been obtained, the patient will be enrolled in the RECOVER study.

Each measurement (S1-S3) consists of a clinical examination, a multicomponent neuropsychological testing, and an MRI protocol. The MRI protocol is designed to acquire both structural (anatomical) data, as well as functional data (see the *Neuroimaging Protocol* section for more details). The clinical examination includes the National Institutes of Health Stroke Scale (NIHSS) [35] and will take approximately 15 minutes. The multicomponent neuropsychological assessment and the MRI scan (including positioning of patient) will each require 45‐60 minutes. A more detailed description is provided in the *Neuropsychological Assessment and Clinical Scores* section. S1 and S2 will be conducted as in-patient measurements, and the S3 3-month follow-up measurement will be conducted as an out-patient measurement.

During the course of the longitudinal study, in particular before S2, the cohort of patients with stroke will be subdivided into 2 groups, those with PSD and those without (non-PSD). Delirium screening using the ICDSC [32] will be conducted throughout hospitalization to identify the onset and duration of delirium. To ensure timely detection of delirium onset and recovery, assessments will be performed every 8 hours. A diagnosis will be made according to the DSM-5 criteria by an independent neurologist, who will review the clinical course alongside the ICDSC data. Delirium recovery is defined as 3 consecutive negative ICDSC screenings.

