### Inclusion and Exclusion Criteria

This study includes patients with stroke with mild-to-moderate stroke symptoms (NIHSS ≤15; eg, [36,37]; Glasgow coma scale [GCS] >8). The prevalence of a PSD increases with age [20], reaching up to 40% among patients aged 60 years and older [1-3]. To ensure an equal distribution into the 2 study groups, only patients aged 60 years or older will be included in the RECOVER study. Textbox 1 gives an overview of all inclusion and exclusion criteria. When patients’ conditions or transfers preclude in-hospital assessment, follow-up visits at patients’ homes will be arranged.

Textbox 1.Inclusion and exclusion criteria for the study enrollment.

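### S2, including its MRI, is set as an in-patient session from day 5, so non-PSD patients discharged home earlier may lack S2 scans and the short-term contrast may be distorted

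*Protocol article*

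**What the plan says.** All references are to the Protocol article.

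- **Setting and timing.** Study Design and General Procedures places S2 at 5 to 14 days after stroke, "depending on delirium recovery", and S3 at about 90 days. On setting it says: "S1 and S2 will be conducted as in-patient measurements, and the S3 3-month follow-up measurement will be conducted as an out-patient measurement".
- **Content.** "Each measurement (S1-S3) consists of a clinical examination, a multicomponent neuropsychological testing, and an MRI protocol". Under Neuroimaging Protocol, the MRI is done on a 3 T whole-body scanner.
- **Who enters.** "This study includes patients with stroke with mild-to-moderate stroke symptoms", with NIHSS 15 or less and no lower limit.
- **Length of stay.** The Abstract (Background) says that "PSD is associated with longer hospitalization, higher mortality, and a higher disability rate". No stay in days is given for either group.
- **Fallback.** Inclusion and Exclusion Criteria adds: "When patients’ conditions or transfers preclude in-hospital assessment, follow-up visits at patients’ homes will be arranged". The Discussion repeats this as a measure against dropout and adds rehabilitation centres.
- **Use of the data.** The study "aims to investigate the short- and long-term effects of stroke and PSD on cognitive outcome". The primary and secondary outcomes are at S3 (Statistical Analysis). The third objective, separating PSD-related from stroke-related impairment with behavioural and fMRI connectivity measures, names no session.

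**The concern.** S1 comes before PSD develops and S3 is at three months, so S2 is the only session that can show short-term effects of PSD. As written, a patient must still be on the ward at day 5 or later to have it. The article itself links PSD to longer stay, so this condition need not act equally in the two groups: PSD patients may stay because of PSD, while a non-PSD patient with a mild stroke may already be at home.

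If the controls who leave early are the better ones cognitively, those left at S2 score too low as a group and a short-term PSD effect is understated. Any S2-to-S3 change would also be measured in a selected control group. Scans that were never acquired cannot be recovered at analysis.

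**Working it through.** The plan gives no figure for S2 completion, so there is none to reproduce. The check has three parts.

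**1. How long must a patient stay to reach S2?** Taking day 5 as 120 h after stroke, stay needed = 120 h − delay from onset to admission.

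| Delay from onset to admission | Stay needed |
|---|---|
| 0 h | 120 h |
| 48 h | 72 h |
| 96 h (limit of the onset criterion) | 24 h |

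Early arrivals need the longest stay. How many controls leave sooner cannot be derived from the article.

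**2. Does another provision cover a control who goes home before S2?**

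- *Home or rehabilitation visits.* These are triggered by condition or transfer. Neither place names S2 or ordinary discharge home. If applied to S2, they can deliver the clinical and neuropsychological parts but not the scan or the in-scanner working memory task.
- *Days post stroke as a covariate (Discussion).* This adjusts for when S2 took place. It does nothing for a patient without S2.
- *Missing-data rule (Statistical Analysis).* It deals with missing tests within a cognitive domain and is not written for a missed session.
- *Dropout discussion.* It expects loss mainly among PSD patients and does not consider early discharge of well controls.

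**3. What could the shift be? Illustration only.** Assume that a share q of the 20 controls, the best on a wellness variable correlated ρ with cognition, misses S2. With c = z(1−q) and φ the standard normal density, the shift in the control mean is −ρ·φ(c)/(1−q) SD. All values of q and ρ are assumptions.

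| q lost | Controls left | ρ = 0 | ρ = 0.3 | ρ = 0.5 | ρ = 1 |
|---|---|---|---|---|---|
| 10% | 18 | 0 | −0.06 | −0.10 | −0.19 |
| 30% | 14 | 0 | −0.15 | −0.25 | −0.50 |
| 50% | 10 | 0 | −0.24 | −0.40 | −0.80 |

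Example for q = 0.3: c = 0.524 and φ(c) = 0.348, so φ(c)/(1−q) = 0.348/0.7 = 0.50. At ρ = 0.5 the shift is −0.25 SD.

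If a share h of those discharged is tested anyway, the shift becomes −ρ·φ(c)(1−h)/(1−q(1−h)). At q = 0.3 and ρ = 0.5:

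- h = 0: −0.25 SD
- h = 0.5: −0.5 × 0.348 × 0.5/0.85 = −0.10 SD
- h = 0.8: −0.5 × 0.348 × 0.2/0.94 = −0.04 SD
- h = 1: 0

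Home visits can therefore remove most of the shift in the behavioural tests. For S2 imaging h stays at 0 unless discharged patients return to the scanner.

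**The case against.** **The in-patient rule is not absolute.** S3 is already out-patient, so a provision for when in-hospital assessment is not possible reads most naturally as one for S2. Nothing bars a discharged patient from coming back for MRI, and sessions may be rescheduled. This stands for the neuropsychological part, where the risk is small if the provision is applied. It does not stand for imaging: a home visit cannot supply it, and the only statement on the setting of S2 is in-patient.

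**No named endpoint is at S2.** The primary and secondary outcomes are at S3, and the prognostic models use S1 predictors of S3 outcome. This stands and limits the weight of the point. What remains exposed is the short-term aim and whatever part of the third objective draws on S2.

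**The direction is not proven.** The Discussion also expects transfers and fluctuating conditions. Losing ill controls would raise the control mean, against the effect described here. Losing ill PSD patients would raise the PSD mean and narrow the contrast further. The net sign is therefore likely but not certain.

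**A stronger reading is tempting.** A reader might infer that well controls will drop out of S2 and that only sicker controls remain, with a bias of known size. The article does not support this: it gives no length of stay or discharge rate, and it offers out-of-hospital visits.

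**A condensed article leaves visit logistics to the full protocol.** That would answer a silence. Here the article states a rule, and the rule itself can cause the loss.

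**Conclusion.** The point holds in a limited form. Making S2 an in-patient session from day 5, in a cohort that includes mild strokes and where PSD is said to lengthen stay, allows S2 attendance to depend on length of stay and so on group. Non-PSD patients who go home before S2 may lack S2 imaging and in-scanner task data. They may also lack S2 neuropsychology if the home-visit provision is not applied to them. The short-term contrast may then be distorted, probably narrowed.

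The size cannot be computed. The tabled shifts, from 0 to −0.80 SD, rest wholly on assumed values of q and ρ and show only how the shift depends on them. The S3 primary and secondary endpoints are untouched by this route. This is a cheap improvement, not a fault in the primary comparison.

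**What to change.** Amend Study Design and General Procedures, and reconcile it with Inclusion and Exclusion Criteria and the Discussion, so that:

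1. a patient discharged before S2 may attend S2, MRI included, as an out-patient within the same 5 to 14 day window;
2. a patient who cannot return is offered a home or rehabilitation-centre visit for the neuropsychological part, with S2 and discharge home named explicitly in that provision.

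Report S2 completion by group, with testing and MRI shown separately, together with the number discharged before S2.

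The cost is wording and some transport. The session and scan are already planned, and out-patient MRI is already part of S3. Some discharged patients will decline to return. In May 2025, 15 of the planned 40 had been included, so 25 were still to come. Recruitment was due to run to September 2025; if it has closed, only the reporting part can still be applied.

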### Inclusion and Exclusion Criteria

This study includes patients with stroke with mild-to-moderate stroke symptoms (NIHSS ≤15; eg, [36,37]; Glasgow coma scale [GCS] >8). The prevalence of a PSD increases with age [20], reaching up to 40% among patients aged 60 years and older [1-3]. To ensure an equal distribution into the 2 study groups, only patients aged 60 years or older will be included in the RECOVER study. Textbox 1 gives an overview of all inclusion and exclusion criteria. When patients’ conditions or transfers preclude in-hospital assessment, follow-up visits at patients’ homes will be arranged.

Textbox 1.Inclusion and exclusion criteria for the study enrollment.
